# **Target Accrual**

We plan to enroll a total of 96 patients who will be randomized with a 1:1 ratio to the interventions (regular saline flushing) or the control (standard of care) arms. We will generate the randomization sequence using a computer program.

# **Enrollment**

The screening and enrollment of subjects will be done by a study coordinator or an investigator who is a member of the RELIEF research team within Vanderbilt or participating institutions. The study coordinator will be responsible for ensuring and reporting subject screening for study eligibility. Once the investigator has determined the subject’s eligibility for the study, the background of the proposed study and the benefits and risks of the study and procedures will be explained to the subject as a part of the consenting process. After consenting, subjects will be considered enrolled if they meet all the inclusion criteria and none of the exclusion criteria. Subjects who fail to meet any of the entry criteria will be excluded from the study and considered a screen failure. Screen failures will be recorded without patient information. Subjects will be able to withdraw from the study at any point.

# **Research Plan and Method**

This will be a randomized trial of patients with chest tubes placed per standard of care for the management of pleural space infection.

The primary objective of this study is to evaluate the impact of regular chest tube flushing on the length of time to catheter removal for patients admitted with pleural space infection who require thoracostomy for the management and clearance of infected pleural fluid.

The secondary objective of this study is to evaluate the impact of regular chest tube flushing on the length of hospitalization for patients, radiographic improvement on chest imaging, the need for additional pleural interventions, and associated complications of chest tube management. We will employ multi-state transition modeling to characterize the role of flushing in longitudinal clinical outcomes and to scrutinize the role of flushing between the two arms in a more granular fashion.

# **Study Procedure**

Patients will be eligible for randomization immediately following and up to 24 hours after chest tube placement. As per the standard of care, patients with a chest tube require a chest X-ray after chest tube placement to assess the proper position of the chest tube. Chest X-ray and ultrasound images obtained at the time of chest tube placement will be reviewed and their information documented as baseline/ day 1. The study team will obtain a baseline assessment of the pleural effusion via ultrasound if no ultrasound images are available within 24 hours prior to chest tube placement).

Subjects will be randomly allocated into intervention (regular flushing) and control (standard of care/flush as needed) groups using computer-generated randomization just prior to starting the procedure.

The intervention groups will have sterile saline 20 mL flushed into their catheter by trained nurses or study team members every 6 ± 2 hours. If patients are receiving tPA/DNase (combined at the same time), each treatment will be considered one flush.

The control groups will have no saline routinely instilled into the chest tube. Instead, chest tube patency will be assessed at least once/day. If the chest tube is considered blocked (lack of tidaling, lack of fluid drainage, and presence of fluid on US exam), the chest tube will be flushed with 20 mL of saline if indicated. All patients in both arms will have -20 cm H2O at the atrium (-80 cm H2O at the wall) continuous suction applied to their drainage system at all times if tolerated.

A daily checklist will be completed by the research team to assess for chest tube blockages and ongoing need for the tube/potential removal of the catheter (see CRF).

On the day of chest tube removal, both the intervention group and control group will undergo a repeat chest X-ray. Post-chest tube removal ultrasound images will be obtained by the research team. Chest X-rays can be performed as portable semi-erect or PA and lateral based on the clinical judgment of the primary provider.

# **Outcomes**

Primary outcome: time from randomization (within 24 hours of chest tube placement) until time to chest tube removal (hours).

Secondary outcomes:

1 – length of hospitalization.

2 – radiographic improvement as evidenced by chest x-ray at the time of chest tube placement compared to the time of removal.

3 – additional surgical procedures for the management of pleural space infection (VATS, additional drains, etc.).

4 – Complications.

# **Design**

Prospective multicenter randomized controlled trial, open label.

# **Data Collection**

The following data will be collected from the records:

1) Demographic data – age, gender, race, smoking status

2) Indication for chest tube placement

3) Date and time of catheter placement

4) Amount of daily fluid drained while in place

5) Imaging data (Chest x-ray and ultrasound images)

6) Length of hospitalization

7) Any instances of deviations from an assigned group (e.g. if a drain was thought clogged and

underwent saline flushing outside of the protocol)

8) Replacement of catheter secondary to dislodgement or inability to drain

9) Presence or absence of continuous wall suction application (for >75% of the previous 24 hours)

10) Date and time of catheter removal

11) Data related to daily chest tube blockage assessment and chest tube removal objective data.

(Because the study investigators and participants are not blinded to the study arm, specific objective criteria (see CRF) for chest tube removal due to successful pleural space infection management will be assessed on daily bases. These data will be documented to assess for change in the behavior of provider due to lack of blinding. This includes categorization of daily drain status, meeting either “successful,” “ongoing” or “”failed criteria.” This data will be used to perform sensitivity analysis to address the potential effects of blinding. Research team members will capture this data.

13) Imaging data on day of chest drain removal (ultrasound, chest-X-ray, or CT scan) characterizing effusion status (Table 2).

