# **Definitions**

A *complicated parapneumonic pleural effusion (CPPE)* is an effusion that has been infected with bacteria or other microorganisms (e.g., positive Gram stain or culture) or biochemical evidence of marked inflammation (e.g., low pH (<7.20), low glucose level (<60 mg/dl), and high lactate dehydrogenase (LDH)).

An *empyema* is a pleural effusion in which frank pus is aspirated from the pleural space.

A *blocked chest tube* is a chest tube that has stopped draining pleural fluid due to particulate material in the lumen of the tube.

A *successful chest tube removal* occurs when the infection in the pleural space has resolved as defined by clinical improvement of the patient and 24-hour fluid output from the chest tube of 150 mL or less.

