# **Multistate Transition Model:**

Our data involves 3 processes: 1) whether patients received tPA/DNase therapy or not, 2) whether patient’s chest tube was deemed clogged vs patent, after appropriate steps taken to unclog a tube, and 3) whether the chest tube ± tPA/DNase was considered a treatment failure, requiring additional invasive procedures. Patients could experience a clogged tube but continue to have ongoing treatment in the form of antibiotics, ongoing drainage, and possible tPA/DNase (as opposed to treatment failure). Patients could transition between states of patent, vs clogged and tPA/DNase free vs tPA/DNase therapy, but if a patient was considered a treatment failure, this state was defined as an absorbing state/terminal state.

Considering these three processes yielded twelve possible states, or categories (see above): 1) patent chest tube with treatment successful, no tPA/DNase (in the past 24 hours), 2) clogged chest tube with treatment successful, no tPA/DNase, 3) patent chest tube with tPA/DNase, treatment successful, 4) clogged chest tube with treatment successful, with tPA/DNase, 5) patent chest tube with ongoing treatment, no tPA/DNase 6) patent chest tube with tPA/DNase with ongoing treatment, 7) clogged chest tube with ongoing treatment, no tPA/DNase 8) clogged chest tube with tPA/DNase with ongoing treatment, 9) patent chest tube with failed treatment, no tPA/DNase 10) patent chest tube with tPA/DNase with failed treatment, 11) clogged chest tube with tPA/DNase with failed treatment and 12) clogged chest tube with failed treatment.

We define four ordinal levels of status based on each category and each patient’s status will be assessed daily from randomization to treatment success, or failure. At any one point, a patient can be within one state, or category, and reaching any absorbing group, defined as treatment success, or treatment failure (groups 1 or groups 4) results in a terminal state with no further transitions possible.

Definition of States**:***Absorbing state* a terminal state, in which the probability of leaving that state is zero. 

*Treatment Successful* notes inpatient effusion management is complete. Chest tube can be removed, and patient could be discharged from a pleural infection standpoint. This does not include those discharged with a chest tube in place for ongoing management.

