*Treatment failed* notes the patient needs an additional procedure for management of their pleural space (e.g., additional chest tube, surgery, etc.).

*Patency of tube* is assessed by the presence of tidaling and/or evidence of ongoing drainage output (*clogged vs. patent)*.

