# **Statistical Considerations**

*Objective and sample size justification*

This is an open label, randomized, multicenter study of the application of flushing for the treatment of pleural space infection among hospitalized patients requiring chest tube drainage. Patients will be enrolled and randomized with a 1:1 ratio to two treatment groups: (1) 20 mL of sterile saline catheter flushing every 6±2 hours with the application of continuous -20 cm H2O suction (2) as needed saline flushing for blockage with the application of continuous -20 cm H2O suction. After enrollment, daily drain patency and criteria for drain removal will be measured and documented. The primary objective of this study is to evaluate the impact of regular chest tube drain flushing on the length of time to catheter removal for patients admitted with pleural space infection who require thoracostomy for their management. Chest tube removal due to chest tube dislodgement or malposition, or “kinking”, and if the patient is deceased with a chest tube in situ, are considered competing risks and will be analyzed as such.

The secondary objective of this study is to evaluate the impact of regular chest drain flushing on the length of hospitalization for patients, radiographic improvement on chest imaging, the need for additional pleural interventions, and associated complications of chest tube management.

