Previous studies have shown a varying number of days to chest tube removal based on etiology, with a mean of 7.6 days (SD: 1.53) in no regular flush populations in a study of 98 patients with infected pleural space (Cafarotti). There is limited data with only one small study reporting median days to chest tube removal (5 days (3-7) in a study of 36 patients with no-flush strategy) (Horsley). Assuming a non-normal distribution, with data skewed to the right, we estimated a median of 6 days to chest tube removal. Assuming a difference of 1 day (24 hours), earlier chest tube removal in the intervention (6 days in the SOC group and 5 days in the intervention group) is a clinical meaningful difference to detect. The sample size is calculated from a two-sided Wilcoxon Rank-Sum test at a 0.050 significance level with a standard deviation of 1.5. Group sample sizes of 38 in each arm achieve 80% power to detect a median difference of 1. The sample size estimation is based on a 2000 Monte Carlo simulation assuming samples from a range of distribution such as Gamma, Lognormal, and Gumbel distributions. Assuming a 10% withdrawal rate and 15% intrapleural enzyme therapy failure (which can prevent reaching the primary endpoint), we plan to enroll 96 Participants (with randomization performed in a 1:1 ratio). To avoid an unbalance in randomization among groups, randomization will be stratified by intrapleural enzyme therapy use.

The main analysis for the outcome will be performed according to the intention-to-treat principle; all the participants with an observed outcome will be included in the analysis according to their assigned trial group.

*Analysis plans*

Continuous variables will be summarized using the mean (SD) or median (range), as appropriate. Frequencies and percentages will be used to summarize categorical variables. The student t-test or the Wilcoxon test will be used to compare continuous variables between two different groups. The chi-square test or Fisher’s exact test will be applied to assess the association between two categorical variables such as complications by treatment.

The Wilcoxon rank sum test will be used to compare time from randomization (within 24 hours of chest tube placement) until time to chest tube removal between two arms among patients who achieved successful chest tube removal.

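### The competing-event list for successful tube removal leaves out treatment failure and removal for blockage

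*Protocol*

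**What the plan says.** The primary outcome (Outcomes) is the time in hours from randomization to chest tube removal, with no reason for removal attached. The analysis narrows this. The t-test or Wilcoxon comparison is made "among patients who achieved successful chest tube removal", and by the Definitions section such a removal "occurs when the infection in the pleural space has resolved as defined by clinical improvement of the patient" together with a 24-hour output of at most 150 mL.

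Statistical Considerations fixes the events that "are considered competing risks and will be analyzed as such" as follows: "Chest tube removal due to chest tube dislodgement or malposition, or “kinking”, and if the patient is deceased with a chest tube in situ". The analysis plans in the same section repeat the same four events and call for a competing-risk regression when they occur.

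Treatment failure is defined under Multistate Transition Model: it "notes the patient needs an additional procedure for management of their pleural space", with an additional chest tube and surgery as the examples. The same section makes failure an absorbing state. The sample size paragraph says that failure of intrapleural enzyme therapy can keep a patient from reaching the primary endpoint, and it allows 15% for this. Item 8 of Data Collection records "Replacement of catheter secondary to dislodgement or inability to drain".

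**The concern.** A competing event is one after which the event of interest can no longer happen. Under the protocol's own definitions, treatment failure is such an event for successful removal of the study tube, and so is taking the tube out because it no longer drains. Neither is on the list. A programmer who follows the list would have to censor these patients at the time of failure or leave them out.

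Censoring treats a patient whose drainage has failed as still able to have a successful removal later, at the same rate as patients still under treatment. Leaving the patient out selects the analysis set on something that happened after randomization. The trial tests whether flushing keeps tubes working, so these endings are among those most likely to differ between arms. The tube losses that are listed (dislodgement, malposition, kinking) are mechanical and have a less direct link to flushing.

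**Working it through.** **Step 1. Set each ending against each analysis in the protocol.**

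| Ending of the study tube | Success-only t-test/Wilcoxon | Competing-event list | Time to failure (Cox, Kaplan-Meier) | Multistate model |
|---|---|---|---|---|
| Removal meeting the success definition | included | event of interest | included, no failure | absorbing, success |
| Dislodgement, malposition, kinking | not a success | listed | not stated | not stated |
| Death with tube in place | not a success | listed | not stated | not stated |
| Additional tube or surgery | not a success | **not listed** | event | absorbing, failure |
| Removal or replacement for inability to drain | not a success | **not listed** | not stated unless it counts as failure | clogged is a non-terminal state |

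The last two rows are the gap. Both endings are foreseen elsewhere in the protocol, and the list is given twice without them.

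**Step 2. Do they preclude the event of interest?** For failure, yes on the plan's own terms: it is an absorbing state, and the sample size paragraph says enzyme therapy failure can prevent the endpoint. For a tube taken out because it does not drain, the study tube is gone without the success definition having been met.

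**Step 3. What censoring would do.** Let f be the share of patients who fail. Suppose, for illustration, that all others eventually have a successful removal.

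- Cumulative incidence of success with failure as a competing event: plateau at 1 − f.
- One minus Kaplan-Meier with failures censored: tends to 1, provided the last tube under observation ends in success.
- With f = 0.15: 1 − 0.15 = 0.85 against 1.
- If the failure shares are f_C (control) and f_F (flushing), the true plateaus differ by f_C − f_F. Under censoring both curves tend to 1 and that difference disappears.

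This holds only under censoring, which the protocol does not state.

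**Step 4. How many patients.** Inputs, all from the sample size paragraph: 38 per arm needed, 10% withdrawal, 15% enzyme therapy failure, 96 enrolled.

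- The plan's figure reproduces as 38 × (1 + 0.10 + 0.15) = 47.5, rounded up to 48 per arm, and 2 × 48 = 96. So the plan applies the 15% to all patients.
- 96 × 0.15 = 14.4, about 14 patients.

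The protocol gives no expected rate of removal for blockage in this trial, so none is added.

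**The case against.** The strongest reply is that failure is not ignored. It is excluded from the t-test or Wilcoxon comparison by a stated rule, allowed for in the sample size, analysed as time to failure in all enrolled subjects, and made an absorbing state in the multistate model. All of that is correct. A reader might infer that failure has no place anywhere in the plan, and the protocol does not support that. The gap is confined to the competing-risk model. Whether the main comparison should be restricted to successes is a separate question.

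Second, event coding usually belongs in the analysis plan, and the daily criteria for successful, ongoing or failed drainage are referred to a case report form that is not shown. This would answer a protocol that was silent. Here the protocol states the list itself, twice, and an analysis plan that added events would depart from it. It is fair that neither list says it is exhaustive, so censoring or dropping is the consequence of following the list, not a stated intention.

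Third, if the model is a cause-specific hazard regression, the hazard ratio for success is the same whether failures are labelled competing or censored. That stands. The coding still matters for cumulative incidence and for a subdistribution hazard model, and leaving patients out affects any of them. The protocol does not name the type of model.

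Three further readings are tempting and go too far:

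- A dislodged and replaced tube may seem to fall in two classes, competing event and failure. This depends on reading a replacement as an additional tube. Data Collection records the two separately, so it is an ambiguity and not an established double classification.
- Discharge with a tube in place may look like another unclassified ending, since the success state says: "This does not include those discharged with a chest tube in place for ongoing management". That sentence defines a state in the exploratory daily model. The tube has not ended; the primary clock runs to removal, and the removal date and time are recorded.
- The Background rates (about one-third needing surgical drainage, 62.8% of drains removed for blockage) might be applied to the 96. They come from other populations, would be applied to both arms alike, and sit beside another cited series with 9% blocked.

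**Conclusion.** The concern holds for the competing-risk model. Its event list, as stated, omits treatment failure and removal or replacement for inability to drain, although both preclude a successful removal of the study tube. It is an error in a stated rule, not a missing detail.

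The size is about 14 of 96 patients. That rests on the plan's 15%, which is an assumption about enzyme therapy failure only, while patients are eligible with or without that therapy. It therefore covers neither failure without enzyme therapy nor removal for blockage, and it would be smaller if applied only to those who receive enzymes. The direction is clear if failures are censored: the cumulative probability of success is overstated. The effect on the comparison between arms depends on how far flushing changes failure and blockage, which the protocol cannot tell us.

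Whether replacing a dislodged tube counts as failure is unsettled, and the passages must be reconciled.

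**What to change.** In both places in Statistical Considerations where competing events are listed, add treatment failure (as defined under Multistate Transition Model) and removal or replacement of the tube for blockage or inability to drain. Fit the competing-risk model in all randomized patients, with successful removal as the event of interest.

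State once, for the primary, time-to-failure and multistate analyses alike, whether replacing a dislodged tube is an additional chest tube in the sense of the failure definition. Either answer can be coded; it should be fixed before outcome data by arm are seen, since the trial is open label.

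The cost is protocol wording and event coding. Replacement, additional tubes, surgery, and removal date and time are already collected, and no change to sample size follows from this point.

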**Table 2. Imaging data collected on day of chest drain removal**

| **Day of Chest Drain Removal: Effusion Classification** |
| --- |
| **Chest X-Ray** |
| 0= no pleural fluid present  1= blunting of the costophrenic angle  2= fluid occupying up to 25% of the hemithorax  3= fluid occupying between 26-50% of the hemithorax  4= fluid occupying between 51-75% of the hemithorax  5= fluid occupying between 76-100% of the hemithorax |
| **Ultrasound** |
| Number of rib spaces occupied by effusion in the:  -Anterior view (#)  -Axillary view (#)  -Posterior view (#) |
| **CT Scan** |
| Effusion characteristics:  -Presence or absence of loculations  Effusion size in non-loculated effusion:  - Scant volume/small  - ≤ 1/4 of hemithorax  - ¼ to ≤½ of hemithorax  - ½ to ≤ 3/4 of hemithorax  - ¾ to almost entire hemithorax |

12) Follow up-Data

1. Other treatment strategies: including presence of additional chest tube in the same pleural space, surgical consult (and if applicable surgery date and interventions).
2. Post hospitalization data: Including date of discharge, status of empyema 4-6 weeks and 3 months after removal, and date of infection resolution on chest imaging
3. Complications: Including procedural and treatment related complications, or study-related complications
4. Patient status at follow-up: To further characterize patient outcomes following discharge after successful chest-tube removal, additional data will be collected regarding patient status at their follow-up visit and characterized based on five scenarios:
   1. Follow-up: resolved infection: Upon clinician follow-up there is no further evidence of residual infection clinically and on imaging and no further need for evaluation or treatment for infection resolution.
   2. Follow-up: surveillance: Upon clinician outpatient follow-up there is clinical concern for potential continued or residual infection despite initial chest tube drainage, requiring further clinical evaluation and potentially further procedures for resolution.
   3. Follow-up: ongoing infection: Upon clinical outpatient follow-up there is clear imaging or clinical signs of ongoing pleural infection despite initial chest tube drainage, actively requiring further management.
   4. Patient lost to follow-up: Following hospital discharge, the patient has been unable to be contacted or not presenting to outpatient appointments.
   5. Patient is deceased: Following hospital discharge, the patient is deceased. If available, cause of death will be documented.

